### Process evaluation

Approximately 30 semistructured interviews (10 at each follow-up time point) with be conducted with intervention participants, or until data saturation, to evaluate intervention usage, comprehension and acceptability. Fifteen SBP group participants (five at each time point) will be interviewed to assess potential study contamination. Interviews will also explore whether participants received any additional risk information or SC advice from healthcare professionals as part of their LHC or during any nodule follow-up. Participants will be purposively sampled by age (≤65 years, >65 years), gender, quit motivation, quit status (at 3 and 12 months) and scan findings (ie, CAC present or absent; emphysema absent, present with areas of normal lung elsewhere or diffusely present throughout both lungs) across all interview time-points where possible. Interviews will be conducted across the 2-year trial recruitment timeframe, face-to-face or by telephone according to preference. Participants will be offered a shopping voucher as an inconvenience allowance.

All SCPs in post will be invited to take part in an interview across the three follow-up time points to explore which aspects of the intervention were perceived to influence change, gain insight into contextual barriers and facilitators of embedding the personalised intervention into practice and intervention fidelity.

Audio-recordings of SCP sessions will take place (10% across both arms) across the 2-year recruitment period to assess intervention fidelity. Sessions to be recorded will be purposefully sampled by SCP, quit motivation (where possible), age (≤65 years, >65 years) and gender (men/women). Fidelity will be ascertained by a trained researcher listening to the audio-recordings and coding the appropriate delivery of materials against SBP and standard care plus personalised risk information. To complement session audio-recordings and SCP interviews, SCPs will be asked to self-report fidelity (intervention elements were delivered as intended) and dose (how much of the intervention was delivered).

All interviews will be audio-recorded using an encrypted recorder with permission, transcribed verbatim and anonymised. The audio recording will be labelled using the participant’s unique identification number assigned during YLST and transferred to an external transcribing service. Audio-files will be destroyed after analysis is complete.

### Economic evaluation

An economic evaluation will assess the cost-effectiveness of the personalised feedback intervention over and above standard care. An NHS perspective will be adopted in line with NICE guidance. We will record and calculate the costs of providing the colocated service, the SBP and the intervention prospectively throughout the trial, in terms of staff time, overheads, pharmacotherapy and other consumables. We will also record patients’ utilisation of primary and secondary healthcare services outside of the trial using a short self-report questionnaire. The primary health outcome in the economic evaluation is assessed in terms of quality-adjusted life years (QALYs). The EuroQoL EQ-5D-3L questionnaire will be used to measure health-related quality of life and calculated QALYs using the area under the curve approach.^34^ Questionnaires will be administered at baseline, 3-month and 12-month follow-up.

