### Data collection

Data collection measures are summarised in table 1.

**Table 1 T1:** Data collection measures in study participants

	Baseline	4 weeks	3 months	12 months
Smoking behaviour (including CO validation if abstinence is reported)	X	X	X	X
Motivation to quit smoking	X	X	X	X
Quit confidence	X	X	X	X
Self-efficacy of quitting smoking	X	X	X	X
Use of smoking cessation support	X			X
Wider healthcare resource use	X		X	X
Response efficacy of quitting smoking		X	X	X
Perceived risk of cancer developing cancer		X	X	X
Cancer worry score		X	X	X
Quality of life (EQ-5D-5L)	X		X	X

CO, carbon monoxide.

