### Economic analysis

An incremental cost-effectiveness analysis will be conducted alongside the trial to assess the cost-effectiveness of the personalised feedback intervention over and above standard on an intention-to-treat basis. An NHS perspective will be adopted in line with NICE guidance.^35^ Costs will be calculated using national average unit costs multiplying the reported level of healthcare resource use. A total healthcare cost profile for all patients in each trial arm is then constructed by adding the costs of the intervention and standard care to the wider NHS costs. The economic evaluation will use validated quit rates at 12 months to estimate the incremental cost per QALY afforded by the intervention over and above SBP. The results presented will indicate the NHS cost of funding the intervention in order to gain one additional QALY at 12 months.

To handle the problem of missing trial data, we will conduct a sensitivity analysis employing Rubin’s multiple imputation method.^36^ Thirty multiple imputation (MI) data sets will be generated using the Multiple imputation (MI) command in STATA v.16. The outcomes of the sensitivity analysis will be used to test the impact of missing data on the results. To account for uncertainty due to sampling variation in cost-effectiveness, we will undertake a non-parametric bootstrapping on the incremental cost and effectiveness with 50 000 replications.^37^ Cost-effectiveness acceptability curves will be plotted based on the bootstrap iterations to show the probability of the intervention being more cost-effective than the standard care over a range of a decision-maker’s willingness-to-pay thresholds.^38^

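### The article names two EQ-5D versions for the same visits and two different sources for the QALYs in the 12-month cost-effectiveness ratio

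*Protocol article*

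**What the plan says.** Three places in the protocol article bear on the health outcome of the economic evaluation, which is a secondary aim under Study aims.

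- **Data collection, Table 1.** The quality-of-life row begins "Quality of life (EQ-5D-5L" and is marked at baseline, 3 months and 12 months.
- **Economic evaluation.** QALYs are named as the primary health outcome, and the text continues: "The EuroQoL EQ-5D-3L questionnaire will be used to measure health-related quality of life and calculated QALYs using the area under the curve approach". The questionnaire times given are again baseline, 3 months and 12 months.
- **Economic analysis.** "The economic evaluation will use validated quit rates at 12 months to estimate the incremental cost per QALY afforded by the intervention" over and above standard best practice. The result is to be expressed as NHS cost per QALY gained at 12 months. This section does not mention EQ-5D.

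**The concern.** Two separate statements conflict.

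The first is the instrument. EQ-5D-3L and EQ-5D-5L are different questionnaires with different response levels, and each needs its own value set. If the scoring used does not belong to the version that participants completed, the utilities are wrong, and so is every QALY built on them.

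The second is the origin of the QALYs. One section builds them from EQ-5D responses over time. The other builds the cost per QALY from validated quit rates. These routes use different data and can give different answers. The effect side of the ratio then also feeds the bootstrap and the acceptability curves, so the ambiguity reaches every cost-effectiveness output. If the route is left open until data are available, it can be chosen with the results in view.

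**Working it through.** The plan states no figure to reproduce here. The check sets the passages side by side and writes out what each would compute.

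**Step 1: EQ-5D version.**

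| Place | Version | Visits |
|---|---|---|
| Data collection, Table 1 | EQ-5D-5L | baseline, 3 months, 12 months |
| Economic evaluation | EQ-5D-3L | baseline, 3 months, 12 months |

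The visits are identical, so the two entries cannot be read as two instruments used at different times. Both versions have five dimensions. With three levels each there are 3^5 = 243 health states; with five levels, 5^5 = 3125. A value set made for one does not fit responses to the other. The table of ethical amendments records no change of quality-of-life instrument that would explain the difference.

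**Step 2: QALYs by area under the curve (Economic evaluation).** Let u0, u3 and u12 be a participant's utilities at 0, 3 and 12 months. With intervals of 0.25 and 0.75 years, the trapezium rule gives:

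QALY = 0.25 × (u0 + u3)/2 + 0.75 × (u3 + u12)/2

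= 0.125 × u0 + 0.5 × u3 + 0.375 × u12

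The weights sum to 0.125 + 0.5 + 0.375 = 1 year. The only inputs are EQ-5D utilities.

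**Step 3: QALYs from quit rates (Economic analysis).** A quit-rate route has the general form:

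QALY difference = (difference in validated 12-month quit proportion) × (QALYs per quitter)

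The first factor will be observed. The second is not given in the article, and neither is a model that would supply it.

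**Step 4: comparison.** The two formulas share no input. If the arms had equal validated quit rates at 12 months, step 3 would give a QALY difference of zero whatever the EQ-5D data showed; step 2 would not. The two sections therefore define different effects under one name.

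**Step 5: role of baseline EQ-5D.** From step 2, a chance difference d between arms in mean baseline utility adds 0.125 × d directly to the QALY difference. If it persisted in full at 3 and 12 months, it would add (0.125 + 0.5 + 0.375) × d = d. Baseline EQ-5D is already collected, so this can be removed by regression.

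**The case against.** The strongest reply is that the Economic evaluation section does fix the effect: it names QALYs, gives the method and gives the visits. The later section keeps the same unit and the same 12-month horizon. On that reading, the quit-rate sentence merely runs together a cost-per-quitter result and a cost-per-QALY result, and the EQ-5D mismatch is a one-character slip.

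This may well be how the text arose, and it explains why the remedy is small. It does not remove the conflict. The sentence as written makes quit rates the input to the cost per QALY, and nothing in the article tells the analyst to disregard it. A slip in the instrument's name still has to be corrected, because the name fixes the scoring.

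Three stronger readings are tempting but not supported.

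- A reader might infer that Table 1 is correct and that following the economic section would mis-score the data. The article does not show which entry is the slip.
- A reader might infer a contradiction between the intention-to-treat basis and the handling of missing data: "To handle the problem of missing trial data, we will conduct a sensitivity analysis employing" multiple imputation. Intention to treat means analysis by allocated group and does not require imputation in the base case. The article never says that the base case uses complete cases; it does not describe base-case handling, which an article may leave to the full protocol or analysis plan. The rule that missing means smoking is stated for abstinence and is not extended to costs or utilities.
- A reader might try to size the effect on the ratio using the 8.6-point difference in the Sample size section. That figure is a detectable difference at 3 months, not an expected one at 12 months. The article gives no utility gain from quitting, no standard deviation of QALYs and no quit-to-QALY conversion, so the two routes cannot be compared numerically.

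**Conclusion.** Wrong as written, on two counts. Table 1 and the Economic evaluation section name different EQ-5D versions for the same visits. The Economic evaluation and Economic analysis sections give different sources for the QALYs, with no link between them. The version conflict lies between the table and the economic text; the QALY-source conflict lies within the economic text.

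The consequence is confined to the cost-effectiveness result. That result's main effect measure cannot be computed consistently from the article, but the primary cessation outcome and its analysis are untouched. No numerical size is claimed. The conclusion rests on the wording of the three places cited and on the trapezium rule being what is meant by area under the curve.

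**What to change.** 1. In Table 1 and in the Economic evaluation section, state the EQ-5D version actually administered and the value set that matches it.
2. Define the effect in the 12-month incremental cost-effectiveness ratio as EQ-5D area-under-the-curve QALYs, with the difference between arms estimated by regression adjusting for baseline EQ-5D. The Statistical analyses section plans no baseline adjustment, so this should be stated as a deliberate choice for the economic outcome.
3. Amend the quit-rate sentence in the Economic analysis section so that validated 12-month quit rates feed a separately reported cost per additional CO-validated quitter, not the cost per QALY.

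The cost is a few lines of wording, one regression and one further ratio. EQ-5D at all three visits and CO-validated cessation at 12 months are already scheduled, so no new data are needed. The changes should be recorded before the economic data are compared by arm.

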#### Non-participants

Eligible participants who attend for an LHC but opt-out of receiving SC support, or receive SC support but do not consent to participate in the YESS study will be asked to complete a brief questionnaire detailing their reasons for declining. Further, individuals who receive SC support but do not consent to participate in the YESS study will be asked to provide consent to be contacted at 3 and 12 months to ascertain smoking status only.

Additionally, we will purposively sample approximately 30 non-participants by quit motivation (where possible), age (≤65 years, >65 years) and gender for interview to understand their reasons for non-participation. Interviews will be carried out face-to-face or by telephone, according to preference, and participants will be offered a shopping voucher. Where possible interviews will be conducted within a 2-week window after declining. We will conduct interviews across the 2-year trial recruitment timeframe. Consent for interviews with those who decline will be obtained via telephone according to a standardised consent script. Information sheets and a copy of the consent script will be sent to participants prior to interview.

#### Comparative measurement in those smokers attending community stop smoking services

Anonymised data will be provided for those aged 55–80 years for dates corresponding to the study period from the local NHSSSS to compare quit outcomes in those receiving SC support through YESS with those accessing community services.

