### Trial design

This is a pragmatic, parallel-group, open, randomised controlled trial comparing an enhanced, personalised SC support package, tailored to include results from LCS, delivered in addition to an SBP cessation package, versus SBP package alone. Further, we will also compare the effectiveness of the colocated service with local stop smoking services (SSS) in an observational design.

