### Randomisation

After the screening visit, but before the 4-week follow-up, all smokers who agreed to see the SCP will be randomised to either continued SBP or intervention using concealed allocation. The randomisation sequence (1:1 in permuted blocks of random size up to size 6) will be generated using a computer random-number generator and participants allocated sequentially, overseen by the University of Nottingham clinical trials unit.

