### SC provision

#### All eligible smokers

Unless explicitly declined, all eligible YLST participants will attend a consultation with a specialist SCP, trained to National Centre for Smoking Cessation and Training standards,^31^ colocated within the screening van. Support will be provided in line with National Institute for Health and Care Excellence (NICE) PH48 guidance^32^ comprising one session of behavioural support at the time of the LHC and provision of pharmacotherapy (either as nicotine replacement therapy through delegated prescribing at the visit and/or a commercially available e-cigarette, or arrange a GP prescription for varenicline or bupropion). Follow-up contact either face-to-face or by telephone, typically weekly but more or less frequently according to participant preference for up to 4 weeks from the date of the LHC.

Where study SCP follow-up is not possible, or if the individual smoker prefers, contact details will be passed to the local NHSSSS for referral into community services immediately following the screening visit.

All eligible participants will be asked for consent to be contacted by telephone at 4 weeks, 3 months and 12 months after the screening visit solely to ascertain smoking status, with optional CO validation if quit. Approximately 4 weeks after the screening visit (and hence after scan results have been issued by YLST), the SCP will arrange a face-to-face visit with the smoker either at home or community location (according to the participant’s preference) to ascertain current smoking status (with CO validation in those reporting abstinence). Informed written consent for participation in the trial will be confirmed at this visit, and individuals treated according to their allocated group as follows:

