#### Secondary outcomes

Self-reported and CO validated continuous cessation at 4 weeks in all eligible smokers agreeing to receive SC from the SCP as part of the LHC.Self-reported continuous and seven day point prevalent SC at 3 months.Self-reported and CO validated continuous cessation at 12 months.Attempts to quit smoking.Changes in psychological variables, including perceived risk of lung cancer, motivation to quit smoking tobacco, confidence and efficacy beliefs (self and response) at all follow-up points.

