#### Comparative measurement in those smokers attending community stop smoking services

We will compare cessation rates at 4 weeks between the intervention and SBP groups with those smokers aged 55–80 attending the local stop smoking service over the same time period to delineate the effect of both SC interventions within YESS, using logistic regression and adjusting for observed baseline differences in predictors of cessation including age, gender, heaviness of smoking and level of education.

A detailed statistical analysis plan will be prepared prior to completion of trial recruitment, and agreed with the trial steering committee.

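### As written, the community-service comparison allows smokers referred from YESS to be counted in the comparator, and the YESS denominator at 4 weeks is not fixed consistently

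*Protocol article*

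**What the plan says.** Under Study aims, the uptake and effectiveness of the colocated service is the first of two primary aims. Under Trial design: "we will also compare the effectiveness of the colocated service with local stop smoking services (SSS) in an observational design".

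**Comparator.** The section on comparative measurement that precedes the statistical part describes the source: "Anonymised data will be provided for those aged 55–80 years for dates corresponding to the study period from the local NHSSSS", in order "to compare quit outcomes in those receiving SC support through YESS with those accessing community services". Under All eligible smokers (SC provision), when the study's smoking cessation practitioner (SCP) cannot follow a smoker up, or the smoker prefers it, "contact details will be passed to the local NHSSSS for referral into community services immediately following the screening visit".

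**YESS side.** The section of the same title under Statistical analyses says: "We will compare cessation rates at 4 weeks between the intervention and SBP groups with those smokers aged 55–80 attending the local stop smoking service". Randomisation says that after screening but "before the 4-week follow-up, all smokers who agreed to see the SCP will be randomised". Blinding and All eligible smokers place trial consent at the 4-week visit. Secondary outcomes defines 4-week cessation "in all eligible smokers agreeing to receive SC from the SCP as part of the LHC", that is, from the lung health check (LHC) onwards.

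**The concern.** Both randomised arms receive the colocated service, so the trial's own randomised comparison cannot show whether that service works better than the usual one. The community comparison is the only comparative evidence the article describes for this primary aim. Two features of it need attention.

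- **Overlap.** The comparator comes from a service into which YESS itself sends smokers. A person could be counted on both sides, or be counted as a community client although first approached and supported on the screening van.
- **Denominator.** If the YESS rate is taken only over people who consented at the 4-week visit, entry to the denominator is decided at the same visit at which the outcome is read. People not reached by then would fall out of the YESS rate.

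The planned adjustment covers baseline predictors such as age, gender, heaviness of smoking and education. It corrects neither selection that happens after baseline nor membership of both groups.

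**Working it through.** The article gives no figure for this comparison, so there is none to reproduce. It also gives neither the share of smokers referred on nor the share reached at week 4. The check is therefore a reading of the sections side by side, followed by illustrative arithmetic.

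**1. Can referred smokers enter the comparator?**
- Referral goes to the local NHS stop smoking service straight after the screening visit (All eligible smokers).
- The comparator is that service's clients aged 55–80 over the study dates.
- YLST participants are aged 55–80 (Participants and recruitment), and referral takes place during the study.

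Referred smokers who take up the service therefore pass both stated filters. No exclusion is stated. With anonymised records, removal is possible only if the service acts, or supplies a referral-source field, before release.

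**2. Who is on the YESS side?**

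| Points to week-4 consenters | Points to all who agreed to or received support |
|---|---|
| Blinding: consent is taken at the 4-week visit | Randomisation: all who agreed to see the SCP are randomised before week 4 |
| All eligible smokers: consent is confirmed at that visit, then treatment follows allocation | Secondary outcomes: 4-week cessation in all who agreed to support |
| Non-participants: supported smokers who do not consent are outside the study, with contact at 3 and 12 months only | Comparative measurement (data section): those receiving support through YESS |
| Statistical analyses: describes people as consented to a group | All eligible smokers: everyone eligible is asked to agree to a 4-week call |

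The analysis section's wording, "We will compare cessation rates at 4 weeks between the intervention and SBP groups", fits either column.

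**3. Size if only week-4 consenters are counted.** Let *a* be the quit rate among those who attend and consent, *f* the share who do so, and *q* the quit rate in the rest.
- Rate over all seen = *a·f* + *q*·(1 − *f*).
- Overstatement = (1 − *f*)·(*a* − *q*).

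Take *a* = 53%. This is the 1-month figure for national NHS services under Sample size, borrowed here as an assumption. *f* and *q* are also assumed.

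| *f* | Rate, *q* = 0 | Overstatement | Odds ratio, 53% vs that rate | Rate, *q* = 20% | Overstatement |
|---|---|---|---|---|---|
| 90% | 0.53 × 0.9 = 47.7% | 5.3 points | 1.24 | 47.7 + 2.0 = 49.7% | 3.3 points |
| 80% | 0.53 × 0.8 = 42.4% | 10.6 points | 1.53 | 42.4 + 4.0 = 46.4% | 6.6 points |
| 70% | 0.53 × 0.7 = 37.1% | 15.9 points | 1.91 | 37.1 + 6.0 = 43.1% | 9.9 points |

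For scale, the randomised comparison is sized to detect 8.6 to 10 points (Sample size).

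**4. Size of the overlap.** Let *c* be the share of comparator records that are YESS referrals and *r* their quit rate. Suppose the service's own clients quit at 53%. The comparator rate moves by *c*·(*r* − 0.53).
- *c* = 5%: 0.05 × (0.20 − 0.53) = −1.65 points at *r* = 20%; 0.05 × (0.60 − 0.53) = +0.35 points at *r* = 60%.
- *c* = 20%: 0.20 × (−0.33) = −6.6 points; 0.20 × 0.07 = +1.4 points.

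The sign depends on *r*, and the effect is small when *c* is small. Only in the special case where referred smokers quit at the YESS rate does overlap shrink the difference by the factor (1 − *c*): a true 10 points would become 9.5 at *c* = 5% and 7.0 at *c* = 30%.

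**The case against.** The strongest reply is that the article is a condensed account. It points to a full protocol and to a detailed statistical analysis plan, neither of which is shown. Extraction filters for an outside dataset could well sit there, and anonymising does not stop the service from filtering first. On the denominator, the article already contains the wider population in Secondary outcomes, and randomisation comes before consent, so the two named groups may simply mean everyone randomised. The comparison is labelled observational, and neither the primary outcome nor the sample size depends on it.

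Much of this limits the point without removing it. A reader might infer that the plan definitely places referred smokers in the comparator and definitely restricts YESS to week-4 consenters. The documents do not support that: the first follows from filters that admit these smokers with no stated exclusion, and the second is one of two readings.

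A reader might also infer that overlap pulls the result towards no difference, or that the result as a whole favours YESS. Neither is established. Referred smokers are those the SCP could not follow or who preferred the community service, and their quit rate could lie on either side. The article does not say how the local service counts clients or treats non-contact. Comparing smokers reached by an opt-out offer with people who use a stop smoking service may also work against YESS.

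What stands is that the stated filters admit the referrals, that the remedy must come before anonymising, and that the sections disagree on the YESS population.

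**Conclusion.** The point holds in a limited form. Following the article as written can contaminate the only comparative evidence for a primary aim, and the population on the YESS side must be reconciled across sections.

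If the narrow reading were applied, the YESS 4-week rate would exceed the rate over all smokers seen by about 3 to 16 points across the assumed range (70–90% attendance, 53% quitting among attenders, 0–20% among the rest). These figures illustrate the mechanism; they are not estimates for this trial. They describe overstatement relative to all YESS smokers seen, not relative to the community service, whose denominator is undocumented. The overlap effect has no known sign or size, because the referred share and these smokers' quit rate are not given. The net bias of the comparison is unknown.

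This should be settled before the data extract is requested. Confidence is medium, because the unseen full protocol or analysis plan may already deal with it.

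**What to change.** - **Data request.** Ask the local service to flag or exclude clients referred from YLST/YESS before it anonymises the records. Keep those smokers in the YESS group, where they started.
- **YESS population.** Align the analysis section with Secondary outcomes: use all smokers who agreed to SCP support at the LHC, pooled over arms. Pooling is coherent at this time point because the booklet is given at the 4-week visit; under the sealed-envelope procedure it is opened only after consent and data collection. The 4-week rate therefore cannot separate the two arms' interventions.
- **Same rules on both sides.** State one denominator rule, and count non-contact as smoking in both groups, as far as the service data allow. Where they do not, say so and report the difference.
- **Follow-up wording.** Reconcile the 4-week call offered to all eligible smokers with the Non-participants section, which lists only 3 and 12 months for those who do not consent.

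The cost is one extra field or filter in the request and a few sentences in the analysis plan. The YESS 4-week quit rate is likely to look less favourable than one computed over week-4 consenters.
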